#### Data collection, access, and management

3.8.5

All information regarding the patient is anonymized through initial processing, and all investigators are obliged to maintain the confidentiality of the results. The source document is registered immediately when the data are collected, and it will be recorded in the CRF. All trial documents will be kept safe, and only those who have been approved by the principal investigator will have access to all the data related to the trial.

The data management for this clinical trial will be conducted in accordance with the standard working guidelines of the Catholic Kwandong University Clinical Research Center, and other matters not specified in the protocol will be conducted in accordance with the International Council for Harmonisation of Technical Requirements for Pharmaceuticals for Human Use (ICH) guidelines for GCP and Korea-GCP standards.

### Statistical analysis

3.9

#### General principle for statistical analysis

3.9.1

An intention-to-treat (ITT) analysis will be performed as the primary analysis for patients who receive acupuncture at least once. A per-protocol analysis will also be performed for participants who have completed the study after excluding dropouts.

For intergroup comparisons, an independent *t* test will be performed for continuous variables if normality is satisfied. If normality is not satisfied, the Wilcoxon rank-sum test, a nonparametric statistical technique, will be performed. For comparisons between different time points within each group, a paired *t* test or Wilcoxon signed rank test will be used. An analysis of covariance (ANCOVA) adjusted for covariant factors that show significant differences with respect to the baseline in each treatment group and the initial baseline outcomes will be additionally determined. For categorical variables, the chi-square test or Fisher's exact test will be used.

All statistical analyses will be two-tailed with a 5% significance level. The last observation carried forward (LOCF) method will be used to handle missing values. Multiple imputation or a regression analysis will be additionally used to examine differences in the results.

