The patients visited the hospital five times for evaluation. The screening (Visit 1, V1) included only those participants who submitted the informed consent form. For screening, the demographic information, medical history, physical examination, vital signs, questionnaire survey, laboratory test, and selection/exclusion criteria will be evaluated. Randomization and group allocation will be performed at screening. Fifty patients were enrolled and randomly divided into two groups. Patients who have passed the screening test will have a TKR and will be hospitalized in ∼2 weeks with usual care or usual care plus acupuncture therapy.

The patients will receive a total of eight acupuncture treatments over 2 weeks after surgery (four sessions between 3 and 8 days after surgery and four sessions between 9 and 14 days after surgery). They will be followed up at 3, 4, and 12 weeks after the end of the intervention. The primary outcomes will be assessed at V1, V10, and Week 4 of follow-up. The safety evaluations include adverse reaction evaluations, vital sign assessments, and laboratory tests. The adverse reaction evaluation will be performed every day during the hospitalization period and continued during follow-up at 3, 4, and 12 weeks after surgery. The vital sign assessment will also be performed daily during the hospitalization period after surgery and at 4 and 14 weeks of the follow-up. Laboratory tests will be performed during screening, at V5 and V9, and at 4 and 12 weeks of follow-up. An economic evaluation will be performed during the treatment period (2 weeks) and at 4 and 12 weeks after surgery and will investigate medical costs and utility (quality of life) to estimate the quality-adjusted life years (QALYs). The Euro-Qol five dimension scale (EQ-5D), a multiattribute health measurement instrument, will be used to assess the quality of life at baseline (Week 1) and at 2 and 4 weeks. Medical costs will also be investigated at baseline (week 1) and at 2, 4, and 12 weeks for a total of four assessments. These evaluations are performed simultaneously with the clinical trial through in-person interviews during the survey period and through in-person interviews, phone calls, and online communication using questionnaires thereafter according to a predefined arrangement with the patient.

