#### Acupuncture treatment group

3.4.2

The Acu-treatment group is treated with acupuncture, in addition to the treatment for the usual care therapy group. A disposable sterilized needle made of stainless steel (0.2 mm × 30 mm, Spring Handle Needle, DONGBANG Medical Co, LTD) will be used for treatment. The acupuncture points for treatment are GB 29, GB 28, BL 38, ST 36, CV 3, SP 9, GB 34, ST 28, SP 10, and ST 34. All the acupuncture points were used on the TKR-operated side for 20 min. The reporting of this randomized study was based on the Standards for Reporting Interventions in Controlled Trials of Acupuncture (STRICTA). The Acu-treatment group will receive eight treatments (four sessions between 3 and 8 days after surgery and four sessions between 9 and 14 days after surgery) over 2 weeks. A licensed doctor of Oriental medicine with formal education in the field and over 5 years of clinical experience and acupuncture will perform acupuncture according to the intervention schedule proposed in the protocol.

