#### Early termination or dropout

3.8.4

The early termination or dropout criteria are as follows:

1.Violation of the inclusion/exclusion criteria2.Withdrawal of consent for participation3.Adverse reactions (including serious adverse reactions)

Adverse reactions refer to undesirable and unintended signs, symptoms, or diseases and do not necessarily have a causal relationship with the interventions administered during a clinical trial. However, since the present clinical trial involves patients who underwent TKR, adverse reactions may be deemed symptoms or side effects caused by TKR at the discretion of the operating surgeon and principal investigator. Symptoms that the principal investigator deems as unassociated with the intervention of this clinical trial are not classified as adverse reactions that occur during this clinical trial.

4.Poor compliance (compliance below 70% in the final compliance assessment) or inability to comply5.Violation of the clinical trial protocol6.Other reasons deemed valid by the researchers7.Diagnosis of an infection in the recovery room

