###### Target subjects

3.9.3.4.1

Patients who participated in the clinical trial at least once starting with V2 will be included in the economic evaluation.

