###### Exceptions to the exclusion criteria for the economic evaluation

3.9.3.4.4

Participants who drop out or are excluded due to the treatment effects or adverse effects of acupuncture or due to the worsening of the disease will be subject to an economic evaluation as long as the evaluation is feasible. The economic evaluation will be continued for the following dropout cases due to treatment effects or adverse effects.Cases: Drop-out due to recovery or loss of symptoms during the treatment period, drop-out due to the adverse effects from a drug, and treatment-related drop-out deemed by our researchers as associated with the target disease or the treatment provided in this clinical trial due to the secondary occurrence of a disease (e.g., surgical site infections, etc).These exceptional cases will be included in the ITT analysis as there is a high possibility that the effect estimates will go missing during the study. The LOCF will again be used to estimate the missing values. However, in cases in which the missing pattern is not monotone, multiple imputation can be used to check the sensitivity.

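### The primary ITT set is limited to patients who received acupuncture: read literally it has no usual-care arm, and read leniently it can exclude patients from one arm only

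*Protocol article*

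**What the plan says.** Section 3.9.1 fixes the primary analysis set: "An intention-to-treat (ITT) analysis will be performed as the primary analysis for patients who receive acupuncture at least once". It adds a second set: "A per-protocol analysis will also be performed for participants who have completed the study after excluding dropouts". The same section and section 3.9.3.1 plan independent t or rank-sum tests between the two groups.

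Section 3.4.2 says who is needled: "The Acu-treatment group is treated with acupuncture, in addition to the treatment for the usual care therapy group". The sessions run as "four sessions between 3 and 8 days after surgery and four sessions between 9 and 14 days after surgery". Section 3.2 places allocation earlier: "Randomization and group allocation will be performed at screening". Screening precedes the operation in Table 1.

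Two other places touch on who is analysed. Section 3.9.3.4.1 says "Patients who participated in the clinical trial at least once starting with V2 will be included in the economic evaluation". Section 3.9.3.4.4, on certain dropouts in the economic evaluation, says "These exceptional cases will be included in the ITT analysis". Neither says that all randomised patients enter the primary analysis, and neither gives a rule for usual-care patients in that analysis.

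**The concern.** A usual-care patient treated as allocated never receives acupuncture and so cannot meet the stated condition. The primary comparison needs both arms, so the sentence contradicts the tests that it is meant to support. It also contradicts its own label, because intention-to-treat does not depend on treatment received.

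The obvious repair is to apply the condition to the acupuncture arm and keep every usual-care patient. That still leaves a one-sided filter. Surgery lies between randomisation and the first session. Section 3.8.4 lists dropout reasons that can fall in that interval, such as withdrawal of consent or an infection found in the recovery room. Participants cannot be blinded (section 3.6), so withdrawal could also depend on the allocation. An acupuncture patient lost in the interval leaves the primary set, while an identical usual-care patient remains. The balance created by randomisation is then no longer guaranteed, although the result would be reported as ITT.

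**Working it through.** **Plan's own figure.** Inputs from section 3.3: difference 3.60, SDs of change 4.05 and 4.16, two-sided alpha 0.05, power 80%, dropout 10%.

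- Pooled SD = sqrt((4.05² + 4.16²)/2) = 4.105.
- The two-sample t calculation gives 21.42 per group, rounded up to 22.
- 22/0.9 = 24.4, rounded up to 25 per group, 50 in total.

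The stated sample size reproduces, and this point does not affect it.

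**Counts under each reading**, with 25 allocated per arm:

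- All randomised, as allocated: 25 versus 25.
- Literal reading of section 3.9.1: up to 25 versus 0, so no between-group test exists.
- Lenient reading: (25 − k) versus 25, where k is the number of acupuncture-arm patients with no session.

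**Effect of the lenient reading.** Let D be the difference in mean K-WOMAC change between the retained and the excluded acupuncture patients. The arm mean over all 25 equals the retained mean minus (k/25) × D, so exclusion shifts the estimate by (k/25) × D. The documents give neither k nor D. I assume k from 0 to 5 and D = 4.1, about 1 SD. Power and rejection rates come from the noncentral t distribution with SD 4.105 and noncentrality = difference / (4.105 × sqrt(1/(25 − k) + 1/25)). Power uses a difference of 3.60. The rejection rate under no true effect uses the shift as the difference.

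| k | Arms | Power at 3.60 | Shift | Share of 3.60 | Rejection rate under no effect |
|---|---|---|---|---|---|
| 0 | 25 v 25 | 85.9% | 0 | 0% | 5.0% |
| 1 | 24 v 25 | 85.2% | 0.16 | 5% | 5.2% |
| 2 | 23 v 25 | 84.4% | 0.33 | 9% | 5.8% |
| 5 | 20 v 25 | 81.5% | 0.82 | 23% | 10.0% |

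For k = 2: 2/25 × 4.1 = 0.328, and 0.328/3.60 = 9%. Doubling D to 8.2 with k = 2 gives 0.66 points (18%) and a rejection rate of 8.4%. The loss of power is small; the issue is bias.

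**Direction.** Table 1 schedules K-WOMAC at V1, V10 and FU2 only. A patient lost before V2 has just the pre-operative score. The LOCF rule in section 3.9.1 would therefore give that patient a change of exactly 0. The documents do not say whether 0 is better or worse than the change other patients show about two weeks after surgery, so the sign of the shift cannot be derived.

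**The case against.** The literal reading cannot be what the authors intended, since the between-group tests need a control arm. The sentence may be a slip for at least one study treatment in either arm. That is plausible, but no section says it. The economic set shows that the authors could write an arm-neutral condition, yet it governs the economic evaluation only. Nor can the matter be left to an unseen analysis plan: the protocol states the set, and states it wrongly.

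The practical effect may also be nil. Table 1 places screening within the week before V2, patients then stay in hospital for about two weeks, and a single session qualifies. This stands: k may be 0.

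Four stronger readings are tempting and are not supported:

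- *The bias favours acupuncture.* Early losses may well have a worse prognosis, but the documents give no outcome for them, and LOCF assigns them 0.
- *The dropout list, including "compliance below 70% in the final compliance assessment", removes patients from the ITT set.* Section 3.8.4 defines no analysis set. Section 3.9.1 removes dropouts only from the per-protocol analysis, and a patient who stops after one session still meets the stated ITT condition.
- *The economic set has the same one-sided filter.* Its entry condition applies equally to both arms, and the exceptions in section 3.9.3.4.4 bring patients back in. Researchers' judgement enters only one of the three listed cases. What can fairly be said is that the section leaves unclear which other dropouts are left out.
- *The distortion is large.* A D of 10 points with k = 2 would give 2/25 × 10 = 0.8, or 22% of 3.60. But 10 points is about 2.4 SD (10/4.105), and nothing in the documents supports it.

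**Conclusion.** The definition is wrong as written and should be corrected before any analysis. This rests only on sections 3.9.1, 3.4.2 and 3.2 and on no assumed number. Literally, the primary comparison cannot be run. On the lenient reading, it permits exclusion after randomisation from one arm only. The readings that make it workable give different sets, and that choice should not remain open once data are seen.

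The numerical harm is not established. It is zero if every acupuncture patient receives a session. It is 0.33 points (9% of 3.60) under the illustrative assumption of two exclusions differing by about 1 SD. The direction is undetermined.

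**What to change.** Replace the sentence in section 3.9.1 with: *The primary (ITT) set is all randomised patients, analysed in the arm allocated, whether or not any session was received.*

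Then add:

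- Any at-least-one-treatment set is named as a secondary (modified) set, with the same condition in both arms, for example attendance at V2.
- Because LOCF gives patients lost before V2 a K-WOMAC change of 0, the primary result is checked with the multiple imputation that section 3.9.1 already foresees.
- Patients who stop acupuncture or fall below the 70% compliance mark stay in the ITT set. They are followed at the visits already in Table 1, with K-WOMAC at V10 and FU2, unless they withdraw consent. No K-WOMAC is added at FU1 or FU3, where Table 1 schedules none.

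The cost is a few sentences in the protocol, and in the analysis plan if one exists, plus the effort of keeping contact with patients who might otherwise be treated as dropouts. It needs no extra patients and no new visits.

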### Sample size calculation

3.3

In this clinical trial, changes in the K-WOMAC will be analyzed and assessed to examine the effect of acupuncture on pain and functional improvements in patients who underwent TKR.

Due to the lack of information about domestic clinical trials to examine the K-WOMAC as a primary outcome for assessing the effect of acupuncture on the knee joint, we referred to a study in which aromatherapy massage was performed on patients with knee arthritis (married women).^[8]^

The changes in the K-WOMAC after 2 weeks of aromatherapy massage or regular massage in the experimental and control groups were −6.10 ± 4.05 and 0.24 ± 4.16, respectively. The difference in the K-WOMAC between the groups was 6.34. In this study, the difference in the K-WOMAC between the experimental and control groups is assumed to be 3.60. We referred to previous studies for standard deviations. The level of statistical significance is set at 0.05 (α, two-tailed), and power (1−β) is set at 80%.

The minimum sample size needed to test the statistical significance was calculated using ‘G∗Power 3.1.9.2’ and was found to be 22 participants per group. Considering a 10% dropout rate, 25 participants per group or a total of 50 participants will be recruited.

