##### Primary outcomes

3.9.3.1

The difference between the K-WOMAC score measured during screening and that measured after the last treatment session (V10) will be determined for each participant. The statistical significance of the difference in the K-WOMAC for each group will be determined using a paired *t* test or Wilcoxon signed rank test with a 5% statistical significance level. The independent *t* test or Wilcoxon rank sum test will be used to determine the statistical significance of the efficacy of acupuncture in each group. The results will be adjusted for covariant factors, which are factors that can affect the results of an analysis.

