##### Secondary outcomes

3.9.3.2

The paired *t* test will be used to analyze the changes in the NRS, risk of falling, and range of motion (ROM) from the baseline to V10 in each group. Student's *t* test will be used to analyze these changes between different groups. A repeated-measured ANOVA will be used to analyze the differences in the changes in all variables, including the K-WOMAC score that occur within a group before the treatment.

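### The plan does not fix whether the unadjusted test or an adjusted result decides the primary K-WOMAC comparison, and its ANCOVA picks extra covariates by baseline significance

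*Protocol article*

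**What the plan says.** All references are to the protocol article.

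- **Section 3.9.1 (general principle).** Arms are compared on continuous variables by an independent t test when the data look normal. Otherwise: "If normality is not satisfied, the Wilcoxon rank-sum test, a nonparametric statistical technique, will be performed". An ANCOVA is described as an additional analysis. It adjusts for the initial baseline outcomes and is also "adjusted for covariant factors that show significant differences with respect to the baseline in each treatment group".
- **Section 3.9.2 (demographic data).** Chi-square and t tests compare the arms at baseline on variables that include sex, age, occupation and medical history.
- **Section 3.9.3.1 (primary outcomes).** The primary variable is each patient's K-WOMAC difference between screening and V10. Paired tests at the 5% level are applied within each arm. Between arms a t test for independent samples comes first, and the alternative is given as: "Wilcoxon rank sum test will be used to determine the statistical significance of the efficacy of acupuncture in each group". The section closes: "The results will be adjusted for covariant factors, which are factors that can affect the results of an analysis". No covariate is named.
- **Section 3.9.3.2 (secondary outcomes).** NRS, fall risk and ROM are compared from baseline to V10. A repeated-measures ANOVA is added for differences in the changes in all variables, K-WOMAC included, "that occur within a group before the treatment".

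**The concern.** A confirmatory comparison needs one result, named in advance, that decides it. Here section 3.9.1 ranks adjustment as additional, while section 3.9.3.1 says the primary results will be adjusted. If the unadjusted and adjusted p-values fall on opposite sides of 5%, the text does not say which one counts. The normality rule adds a second data-dependent choice, which also changes what is estimated: a difference in means or a shift in ranks.

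The rule for further covariates is weak in itself. In a randomised trial a significant baseline difference is a chance event, and its p-value says nothing about whether the variable predicts K-WOMAC at V10. Prognostic value, judged beforehand, is the proper criterion. The strongest candidate is baseline K-WOMAC, which the plan already holds, but only in the additional analysis.

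Two pieces of wording make this worse. Paired tests within an arm cannot show an effect of acupuncture, because every patient changes through surgery and recovery; yet they stand beside the between-arm test, which is itself phrased as efficacy in each group. The repeated-measures sentence, as written, describes neither a comparison of arms nor a period after treatment.

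**Working it through.** **1. Reproduce the plan's sample size (section 3.3).** Inputs: "The level of statistical significance is set at 0.05 (α, two-tailed"), power 80%; "the difference in the K-WOMAC between the experimental and control groups is assumed to be 3.60"; changes in the reference study "were −6.10 ± 4.05 and 0.24 ± 4.16, respectively".

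- Pooled SD = √((4.05² + 4.16²)/2) = 4.105; d = 3.60/4.105 = 0.877.
- Two-sample t test, noncentral t: power 81.1% at 22 per arm and 79.2% at 21, so 22 is needed.
- 22/0.90 = 24.4, rounded up to 25 per arm, 50 in total. The plan's figures reproduce.

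**2. Covariates entering by chance.** With m independent baseline variables tested at 5%, the chance that at least one is significant is 1 − 0.95^m. For the four variables named in section 3.9.2: 1 − 0.95⁴ = 0.185, about 19%. That list is introduced as non-exhaustive, so the true number may be larger. Ten variables would give 1 − 0.95¹⁰ = 40%, but ten is not a number in the document.

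**3. Type I error.** Simulation with 22 per arm, 4,000 trials per scenario, normal data and no effect, for correlations 0.3, 0.5 and 0.7. Normality was checked by Shapiro-Wilk in each arm (an assumption; the plan names no criterion).

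- The check switched to Wilcoxon in about 9–10% of trials although the data were normal.
- The t-or-Wilcoxon procedure rejected in 5.3–5.7%. The simulation standard error is √(0.05 × 0.95/4000) = 0.3 points, so this is close to nominal.
- Claiming success if either that procedure or the baseline-adjusted ANCOVA was significant rejected in 7.5–8.2%.

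**4. Power of the baseline-adjusted ANCOVA.** Let r be the correlation of screening and V10 K-WOMAC and k = SD(V10)/SD(screening). The document gives neither, so both are assumptions. Relative to the change score, the ANCOVA residual variance is

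k²(1 − r²)/(1 + k² − 2rk),

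which is (1 + r)/2 when k = 1. Holding the change-score SD at 4.105, the difference at 3.60 and 22 per arm (41 degrees of freedom):

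| k | r = 0.3: ratio, power | r = 0.5: ratio, power | r = 0.7: ratio, power |
|---|---|---|---|
| 0.75 | 0.46, 99% | 0.52, 98% | 0.56, 97% |
| 1 | 0.65, 94% | 0.75, 91% | 0.85, 87% |
| 1.5 | 0.87, 86% | 0.96, 82% | 1.00, 81% |
| 2 | 0.96, 83% | 1.00, 81% | 0.93, 84% |

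The reference is 81% for the unadjusted t test on change. With k = 1 the gain also shrinks as r nears 1 (83% at r = 0.9).

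**5. Skewed data.** In the same simulation with strongly skewed (lognormal) errors and a true difference of 3.60:

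| r | t-or-Wilcoxon | ANCOVA |
|---|---|---|
| 0.3 | 89% | 92% |
| 0.5 | 92% | 90% |
| 0.7 | 94% | 87% |

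ANCOVA is ahead only at r = 0.3.

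**The case against.** The strongest reply is that the planned test is sound. A t test on change is valid under randomisation, it is the test on which section 3.3 is built, and it reaches the stated 80% power. Not choosing a more efficient test is no error, and an article may leave a covariate list or a normality criterion to a fuller document. This stands as far as the t test goes, so the power gain is an improvement on offer and does not show that the trial is too small. It does not answer the main point. The article does state a rule for choosing covariates, and that rule is poor; and its two sections disagree on whether the primary result is adjusted.

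Four stronger readings are tempting, and the document does not support them.

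- *Baseline K-WOMAC is left out of the adjustment.* Section 3.9.1 puts the initial baseline outcomes into the ANCOVA whatever the baseline tests show. Significance-based selection concerns the further covariates only.
- *Data after V10 have no between-arm analysis.* The general rule in section 3.9.1 covers intergroup comparisons of continuous variables without a limit on visits. Section 3.8.2 defines the secondary outcomes as changes from baseline out to day 84. Section 3.9.3.2 is unclear but does not cancel this.
- *The normality switch breaks the 5% level.* On its own it barely moves it. The 7.5–8.2% arises only if success on either result is accepted, and the plan states no such rule.
- *ANCOVA is always more powerful.* That fails when the V10 SD is much larger than the screening SD, and against Wilcoxon under strong skew.

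**Conclusion.** The point holds in a limited form. What the text itself establishes is that the result deciding the primary K-WOMAC comparison at V10 is not fixed, and that further ANCOVA covariates are chosen by baseline significance. The latter would admit at least one of four independent variables by chance in 19% of trials.

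The type I error cost depends on conduct: near nominal if the t-or-Wilcoxon result is always the one that counts, about 7.5–8.2% if either result could be claimed.

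Promoting the baseline-adjusted ANCOVA would raise power from 81% to about 94%, 91% or 87% for r = 0.3, 0.5 or 0.7 with equal SDs. The gain is larger if the V10 SD is the smaller one, and lies between 0 and 5 points if it is 1.5 or 2 times the screening SD. Since screening precedes surgery and V10 follows it, equal SDs cannot be taken for granted. The sample size is correct on its own inputs. The plan should be changed, but nothing here invalidates the design.

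**What to change.** - **Primary analysis (sections 3.9.1 and 3.9.3.1).** Name one: ANCOVA of K-WOMAC at V10 on arm and baseline K-WOMAC, reported as an adjusted mean difference with a 95% confidence interval. Name any further covariates now, on prognostic grounds.
- **Covariate selection.** Delete the choice of covariates by baseline p-values.
- **Sensitivity analyses.** Report both the unadjusted t test on change and the Wilcoxon test, whatever the normality check shows, and drop that check as the gate to the primary result.
- **Within-arm tests.** Label the paired tests as descriptive, and word the primary test as a comparison between arms.
- **Repeated measures (section 3.9.3.2).** Replace the ANOVA sentence by a model with arm, visit, arm-by-visit and baseline value, over the post-baseline visits at which Table 1 collects each outcome: for example V10 and FU2 for K-WOMAC, V10 and FU3 for fall risk.

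The cost is a change of wording before unblinding. It needs no new data, visits or patients.

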#### Primary outcome

3.8.1

The primary outcome in this study was the changes from the baseline in the K-WOMAC. The time frame was as follows: screening, day 11 (visit 10, V10), and day 21 (follow-up 2, FU2). The K-WOMAC^[9]^ was used to evaluate the physical function. The WOMAC is an index that evaluates the pain and functional status of patients with degenerative knee arthritis and is widely used as a measure for evaluating symptoms and treatment effects in patients with degenerative knee joints. It is a self-administered questionnaire consisting of 24 items divided into 3 subscales.^[9]^

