###### Handling the data from dropouts

3.9.3.4.3

For drop-outs, the last obtained measurements will be used for all the remaining visits to make it seem as if the measurements were obtained during those visits (LOCF: last-observation-carried-forward analysis).

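### With LOCF as the main missing-data rule and no K-WOMAC between the pre-operative visit and V10, a patient without V10 is analysed as having exactly zero change

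*Protocol article*

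**What the plan says.** - **Missing data (3.9.1).** "The last observation carried forward (LOCF) method will be used to handle missing values". The next sentence reads: "Multiple imputation or a regression analysis will be additionally used to examine differences in the results". LOCF is thus the main rule and the other methods are checks on it.
- **Assessment times (3.2).** "The primary outcomes will be assessed at V1, V10, and Week 4 of follow-up". The K-WOMAC row of Table 1 has the same three marks. Section 3.8.1 agrees on the visits: "The time frame was as follows: screening, day 11 (visit 10, V10), and day 21 (follow-up 2, FU2").
- **Order of events (3.2).** "Patients who have passed the screening test will have a TKR", so the V1 score is pre-operative.
- **Primary contrast (3.9.3.1).** "The difference between the K-WOMAC score measured during screening and that measured after the last treatment session (V10) will be determined for each participant".
- **Economic evaluation (3.9.3.4.3).** "For drop-outs, the last obtained measurements will be used for all the remaining visits to make it seem as if the measurements were obtained". Section 3.9.3.4.4 uses LOCF again for its exceptional dropouts and allows multiple imputation as a sensitivity check.
- **Costs (3.2).** "Medical costs will also be investigated at baseline (week 1) and at 2, 4, and 12 weeks for a total of four assessments".

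**The concern.** LOCF needs an earlier value that says something about the missing one. Here the only K-WOMAC before V10 was taken before both the knee replacement and the study treatment. Carrying it to V10 asserts that a patient about two weeks after a knee replacement scores exactly as before it. This holds even for a patient who misses V10 but attends FU2. The fall-risk tests (V1, V10, FU3) have the same gap.

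Three things are at stake:
- Equal loss in both arms shrinks the estimated difference and usually inflates the variance.
- Unequal loss biases the estimate. The direction depends on which arm loses more and on whether scores on average rise or fall.
- The filled-in zeros count as observed data in the standard error.

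Unequal loss is plausible: treatment is open-label, only one arm has acupuncture sessions, and section 3.8.4 lists adverse reactions and inability to comply as grounds for leaving.

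**Working it through.** **Inputs from section 3.3.** Difference 3.60; SDs of change 4.05 and 4.16 in the reference study; two-sided alpha 0.05; power 80%; 22 per group, 25 after 10% dropout.

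**The plan's own figure.** Pooled SD = sqrt((4.05² + 4.16²)/2) = sqrt(16.854) = 4.105. The two-sample t test (noncentral t) then needs 22 per group (power 81.1%), and 22/0.90 = 24.4, rounded up to 25. The stated sample size is reproduced.

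**Assumptions, because the document is silent.** The control arm has mean change m and the acupuncture arm m − 3.60, with SD 4.1 in both. Negative m means improvement. I vary |m| from 0 to 20 points. Of 25 patients per arm, k have no V10 and are set to 0.

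**Equal loss, 2 per arm.**
- Expected difference: 3.60 × 23/25 = 3.31.
- Variance in an arm with mean μ and share d = 2/25 = 0.08 of zeros: approximately (1 − d)σ² + d(1 − d)μ².
- At m = −10, control: 0.92 × 16.81 + 0.0736 × 100 = 22.8.
- At m = −10, acupuncture: 0.92 × 16.81 + 0.0736 × 13.6² = 29.1.
- Pooled SD: sqrt((22.8 + 29.1)/2) ≈ 5.1, against 4.1 without the zeros.

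**Power by simulation.** The plan uses the t test if normality holds and the Wilcoxon rank-sum test otherwise. It names no normality test, so I assume Shapiro-Wilk in each arm. Repeat runs agree to about one percentage point.

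| Missing V10 per arm | Mean improvement | t test always | Plan's rule |
|---|---|---|---|
| 2 and 2 | 0 | 83% | 83% |
| 2 and 2 | 5 | 76–77% | 78% |
| 2 and 2 | 10 | 64% | 69% |
| 2 and 2 | 20 | 24% | 72% |
| 1 and 1 | 10 | 75% | 76% |
| 3 (acupuncture) and 2 | 10 | 40% | 52% |

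Observed cases only, 23 per arm: about 83%. At 20 points the zeros lie so far out that normality is rejected in essentially every trial. The rank test then applies and recovers most of the power.

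**Unequal loss, real effect.** With 3 acupuncture and 2 control values missing at m = −10: 13.6 × 22/25 − 10 × 23/25 = 11.97 − 9.20 = 2.77 instead of 3.60.

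**Unequal loss, no effect.** With 4 against 1 missing, the spurious difference is (4/25 − 1/25) × |m| = 0.12 × |m|. That is 1.2 points at a 10-point change and 2.4 points at 20. The simulated type I error is about 8% instead of 5%.

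**Costs.** Copied literally, the week-2 record of a patient lost after week 2 is entered again at weeks 4 and 12: three entries where one was observed, or two within the 4-week initial analysis of section 3.9.3.4.2.

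**The case against.** - **The extreme power loss does not apply.** A reader might infer that power could fall to 24%. That assumes a t test throughout. Sections 3.9.1 and 3.9.3.1 switch to the Wilcoxon test when normality fails, and the figure is then about 72%. This objection stands.
- **The harmless case is real.** If the mean change is near 0, almost no power is lost. The only control-group change in the document is 0.24 (section 3.3), although it comes from a massage study, not from knee replacement. This stands as a limit on size.
- **Much dropout may fall after V10.** Patients stay in hospital for about two weeks, V10 falls around discharge, and the 10% allowance is not tied to V10. With one missing per arm at 10 points, power is about 76%. The 4-against-1 case needs 16% of one arm to miss V10. This also stands.
- **Not every missing primary outcome becomes zero.** Section 3.8.1 also lists FU2. A patient with V10 but no FU2 carries V10, which is not a zero change. The artefact is exact only for the screening-to-V10 contrast.
- **Costs.** A reader might infer that the plan certainly counts the in-patient period again. Section 3.9.3.4.3 speaks of measurements and does not name costs, and section 3.9.3.4.2 takes in-institution costs from electronic records, so these need not be missing. The carried value could also be too low if only the baseline record exists. This part is an ambiguity to settle.
- **Checks are planned.** Multiple imputation or regression, and a per-protocol analysis, would show whether LOCF drives the result. They do not change which analysis is primary.

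**Conclusion.** The point holds for the primary contrast and should be fixed. The zero follows from the document's own rule and schedule, whatever an unseen analysis plan adds. Its size is uncertain. With 2 missing V10 values per arm, the power loss runs from nothing at a mean change near 0 to about 14 percentage points at 10 points (83% to 69%), and is about 11 points at 20. Unequal loss matters more, because it moves the estimate itself: 3.60 falls to about 2.8 with 3 against 2 missing at a 10-point improvement, and 1.2 to 2.4 spurious points arise with 4 against 1 missing and no effect.

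These figures rest on an assumed mean change, an assumed number of missing V10 values, normal changes with SD 4.1, and Shapiro-Wilk as the normality check. The document supports neither a collapse of power nor a certain double-counting of costs.

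**What to change.** 1. In section 3.9.1, make one of these the primary K-WOMAC analysis: multiple imputation by arm, using the NRS (V2, V6) and ROM (V6) already in Table 1 as auxiliaries; or a likelihood-based model of V10 and FU2 adjusted for baseline K-WOMAC, fitted to all observed post-operative values.
2. Keep LOCF at most as a sensitivity analysis, and treat the fall-risk tests in the same way.
3. In sections 3.9.3.4.3 and 3.9.3.4.4, state that LOCF does not apply to costs, which accrue per period. Use electronic records where available and multiple imputation per period otherwise.

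No visit, patient or measurement is added, and the plan already names multiple imputation. The price is a little more analysis work and slightly wider intervals that reflect the missing information honestly.
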